### Intervention

#### Intervention programme

The lifestyle intervention programme is an adapted version of previous work of HealthPartners in Minnesota, USA [13]. This Dutch version of the lifestyle programme is called "Leef je Fit". The programme is based on social cognitive theory [17] and emphasizes 1) identifying behaviours in need of change, 2) setting goals for change, 3) monitoring progress, 4) modifying environmental cues to facilitate change, and 5) modifying consequences to motivate change. An essential part of the programme is coaching on these activities by a personal counsellor.

The programme consists of ten lessons or 'modules'. These provide information on nutrition and physical activity, and teach techniques for changing behaviour (e.g., self-monitoring). Assignments in the modules assist in applying these techniques. The programme can be worked through either at work or at home.

Participants are asked to study a module and finish the assignments every two weeks, so they are able to finish the programme within six months. After finishing each module, participants are contacted by their counsellor. Counselling is done according to two comparable standardized counselling protocols (i.e., for the two communication methods).

Next to the programme materials, the participant receives a pedometer at the start of the programme.

#### Phone intervention

Programme materials for the phone group are provided after randomisation. The employee receives a binder with the ten modules, and the same brochures that are given to the control group. The intervention starts when the personal counsellor first calls the participant, about two weeks after randomisation. In this first contact the counsellor explains the workings of the programme and sets a time and date for the next contact in which the first module will be addressed. In between these contacts, the employee studies the module and fills out the assignments. The counsellor calls the employee at the scheduled date and time, to go through the module and to talk about the assignments according to the standardized protocol. At the end of the call, a new date and time are set for the next call about two weeks later. This interactive process continues until the employee completes all modules, or until the participant declines contact. Participants also have the possibility to contact their counsellor by phone between modules, if they have additional questions.

#### Internet intervention

A website is developed for the intervention. The internet-based lifestyle intervention starts when the employee receives a welcome e-mail, about two weeks after randomisation, with a unique username and password. The first time an employee logs on to the site, he is directed to an introduction which explains the workings of the programme. The employee is asked to fill out some personal details for the counsellor. The employee then starts with the first module. The assignments are filled out on the site and stored in a personalized area of the website. The personal counsellor receives an alert when the employee has finished a module. The counsellor then checks the assignments and comments on them through e-mail within 5 working days, according to the standardized protocol. One week after finishing a module, the participant is able to start with the assignments of the next module. Modules have to be worked through in the given order.

When an employee does not log on to the website according to schedule, he receives an e-mail reminder twice a week. These reminders are continued for the full duration (i.e., six months) of the programme. Besides being reminded by e-mail, employees can also choose to be reminded by text message on their mobile phone.

Participants have the possibility to e-mail their counsellor between modules, if they have additional questions.

#### Counselling

Four counsellors with a degree in nutrition or physical activity provide coaching for the participating employees. Prior to the start of the intervention, they receive a four week training. The counsellors are made familiar with the principles behind the programme and go through the intervention materials. A psychologist trains them in counselling techniques. A pilot group is put together to give the counsellors the opportunity to practise with the counselling protocols, counselling skills and administrative procedures.

Counselling takes place according to a standardized protocol, which is developed for each communication method. Both protocols are similar to each other in approach.

The protocol for the phone-condition consists of a timed outline for each module and provides the counsellors with guidelines on how to counsel the assignments.

The protocol for the internet-condition consists of a semi-prepared e-mail for each module. The e-mail discusses the module by giving generic comments. To this the counsellor adds the answers the participant has filled out in the assignments and addresses those individually in the same manner as in the phone calls.

In order to keep track of appointments, purport of phone calls and e-mails, and the progress of the participants, a web-based participant management system is developed. Counsellors have access to the assignments and progress from the internet group through this participant management system.

### Outcome measures, confounding- and mediating variables

Primary outcomes of the study are 1) weight change and change in BMI, 2) change in physical activity level, and 3) change in dietary intake of fat, fruit, vegetables, sugar and alcoholic beverages. Effects in both intervention groups combined against the effects in the control group are studied, as well as effects in the phone group against effects in the internet group.

Besides these primary outcomes, other outcomes are studied also. Among those are changes in waist circumference, sum of skin folds, blood pressure, total blood cholesterol and aerobic fitness. Other outcomes that are studied include change in work performance/productivity, perceived health, empowerment, stage of change and self efficacy concerning weight control, physical activity and eating habits. Changes in direct medical costs and changes in indirect costs for sickness absence and loss of work productivity are studied as well.

In conclusion, a process evaluation of the execution of the intervention and of participant satisfaction is carried out after completion or the intervention.

Assessment of the aforementioned outcomes, is done either by questionnaire or by physiological measurements. Physiological measurements take place at the work site or near the work site. Questionnaires are sent to the home address of the participant. The scheduling of all measurements is shown in Table 1.

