**Methods/Design:**

ALIFE@Work is a controlled trial, with randomisation to three arms: a control group, a phone based intervention group and an internet based intervention group. The intervention takes six months and is based on a cognitive behavioural approach, addressing physical activity and diet. It consists of 10 lessons with feedback from a personal counsellor, either by phone or e-mail, between each lesson. Lessons contain educational content combined with behaviour change strategies. Assignments in each lesson teach the participant to apply these strategies to every day life.

The study population consists of employees from seven Dutch companies. The most important inclusion criteria are having a body mass index (BMI) ≥ 25 kg/m^2 ^and being an employed adult.

Primary outcomes of the study are body weight and BMI, diet and physical activity. Other outcomes are: perceived health; empowerment; stage of change and self-efficacy concerning weight control, physical activity and eating habits; work performance/productivity; waist circumference, sum of skin folds, blood pressure, total blood cholesterol level and aerobic fitness. A cost-utility- and a cost-effectiveness analysis will be performed as well.

Physiological outcomes are measured at baseline and after six and 24 months. Other outcomes are measured by questionnaire at baseline and after six, 12, 18 and 24 months.

Statistical analyses for short term (six month) results are performed with multiple linear regression. Analyses for long term (two year) results are performed with multiple longitudinal regression. Analyses for cost-effectiveness and cost-utility are done at one and two years, using bootstrapping techniques.

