#### Other outcome measures

Perceived health and empowerment are respectively assessed with the RAND-36[29] and the Mastery Scale of Pearlin [30]. Stage of change in relation to weight control, physical activity and eating habits is assessed using questions about intentions to start changing these behaviours [31-33]. The behavioural determinant self efficacy, concerning weight control, physical activity and eating habits is assessed with a set of questions developed for this study.

The cost-effectiveness and the cost-utility of the lifestyle programme will be ascertained. The cost-effectiveness analysis will be performed from both a company perspective as well as from a societal perspective. The primary outcome measures weight change, change in physical activity level, and change in dietary intake will be included in this cost-effectiveness analysis.

For the company perspective, intervention costs will be compared with obtained benefits from reduced sickness absence and increased work productivity. Intervention costs include costs for the development of the intervention, such as the development of the website and the binders, and costs for the implementation of the intervention, such as salary costs of the counsellors and costs for hosting the website. Self-reported sickness absence is prospectively measured by keeping a six-monthly diary. On a monthly basis the employee records full days absence from work due to sick leave. Diaries are provided at the start of each six month measuring period. In addition, data on sickness absenteeism will be derived from employer records, from six months before baseline till two years after baseline. Work productivity is measured with the work related questions from the WHO Health and Work Performance Questionnaire (HPQ) [34]. Work productivity assessed by the HPQ is based on self-report. The HPQ is validated and available in several languages, including Dutch.

The cost-effectiveness from a societal perspective will be addressed by assessing health care utilization and medical costs. Health care utilization is based on actual resource use, using prospective data collected by a diary in which the employee records use of medical services and medication on a monthly basis. This diary is combined with the diary recordings on sickness absence. Direct medical costs of health care utilization are calculated using cost prices if available and otherwise tariffs will be used.

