### Statistical analyses

Baseline values will be analysed for differences in the three groups, by one-way-analysis of variance for numerical data and chi-square for categorical data.

Analyses for the primary outcomes, for the physiological outcomes and for the other outcomes (e.g., perceived health) will be at six months (short term) and after two years (long term). They will be performed according to the intention-to-treat principle. Analyses for short term results will be performed with multiple linear regression. Analyses for long term results will be performed with multiple longitudinal regression.

Bootstrapping will be used for comparison of mean direct, indirect and total costs between groups [36]. Confidence intervals for the mean difference in costs will be obtained by bias corrected and accelerated bootstrapping. Cost-effectiveness ratios and cost-utility ratios will also be calculated with bootstrapping according to the bias corrected percentile method. Separate cost-effectiveness ratios will be calculated for the primary outcomes [37]. Bootstrapped cost-effect pairs will be graphically represented on a cost-effectiveness plane [38]. Acceptability curves will be calculated, which show the probability that a treatment is cost-effective at a specific ratio.

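### The cost outcome is named as changes in costs, but no pre-randomisation medical cost is described and the analysis compares mean costs; pre-baseline absence records have no stated use, although they could sharpen the absence-cost comparison

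*Protocol article*

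**What the plan says.** **Outcome.** Under Outcome measures, confounding- and mediating variables, the article lists the cost outcomes as follows: "Changes in direct medical costs and changes in indirect costs for sickness absence and loss of work productivity are studied as well".

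**Data sources**, all under Other outcome measures:
- Health care use is measured "using prospective data collected by a diary in which the employee records use of medical services and medication on a monthly basis". Of the same diary the article says: "This diary is combined with the diary recordings on sickness absence". On timing: "Diaries are provided at the start of each six month measuring period".
- Absence is also taken from employers: "data on sickness absenteeism will be derived from employer records, from six months before baseline till two years after baseline".
- Work productivity comes from the HPQ, a self-report questionnaire. The abstract schedules questionnaires at baseline and at 6, 12, 18 and 24 months.

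**Analysis.** Under Statistical analyses: "Bootstrapping will be used for comparison of mean direct, indirect and total costs between groups". Then: "Confidence intervals for the mean difference in costs will be obtained by bias corrected and accelerated bootstrapping". The abstract and the Discussion place the economic analyses at one and two years.

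**The concern.** Two statements in the same article describe different quantities. In the outcomes section, change is also the word used for weight, waist circumference, blood pressure and productivity, all of which have a baseline value. A reader will therefore take a change in medical costs to mean a change from baseline, yet no baseline medical cost is described. The analysis section instead describes a difference in mean costs between groups, which needs no baseline.

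The second matter is separate. Absence costs enter the company-perspective result, and a pre-randomisation measure of absence is being collected. The stated cost analysis is a plain comparison of means, and the list of possible confounders does not include prior absence. Precision that the data could provide may go unused.

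**Working it through.** **The plan's own figure.** No design figure is given for costs. The only calculation, under Sample size, concerns weight: SD 6.8 kg, difference 1.4 kg, two-sided 0.05, 90% power. It reproduces at 496 per group against the stated 500 (power 90.2% at 500) and has no bearing here.

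**Step 1: which cost components have a baseline in the visible text?**

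| Component | Source | Value before randomisation described? |
|---|---|---|
| Direct medical costs | Prospective diary | No |
| Sickness absence | Diary and employer records | Yes, employer records from month -6 |
| Work productivity | HPQ questionnaire | Yes, questionnaires start at baseline |

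The gap is therefore confined to direct medical costs.

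**Step 2: what would a diary-only change measure?** The first diary is read here as covering months 0-6, which fits the 0/6/12/18/24-month schedule. On the programme the abstract says: "The intervention takes six months and is based on a cognitive behavioural approach, addressing physical activity and diet". It starts about two weeks after randomisation, so the first diary largely coincides with it. Take an assumed between-group cost difference, in arbitrary units per six-month period:

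| Pattern over the four periods | Difference in 0-24 month total | Last diary minus first diary |
|---|---|---|
| -100, -100, -100, -100 | -400 | -100 - (-100) = 0 |
| -100, 0, 0, 0 | -100 | 0 - (-100) = +100 |
| 0, -100, -100, -100 | -300 | -100 - 0 = -100 |

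The cumulative difference is the quantity an economic evaluation needs. A change from the first diary can cancel it or reverse its sign. This shows why the word is unsuitable; it does not describe a planned analysis.

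**Step 3: what would pre-baseline absence add?** Let r be the within-arm correlation between absence in the six months before baseline and absence cost in follow-up. In a regression on arm and prior absence, the variance of the arm difference is about (1 - r²) times the unadjusted variance, and the interval width is √(1 - r²) times the unadjusted width. The documents give no r; these values are assumptions.

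| Assumed r | Variance cut, r² | Width ratio, √(1 - r²) | Interval narrower by |
|---|---|---|---|
| 0.3 | 9% | 0.954 | about 5% |
| 0.4 | 16% | 0.917 | about 8% |
| 0.5 | 25% | 0.866 | about 13% |

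**The case against.** The strongest reply is that the analysis is already right. A comparison of mean costs between randomised groups is valid without baseline costs, and the article says that this is what will be done. That stands, and it limits the first matter to wording.

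Four stronger readings are tempting, and the document does not support them:
- *That any effect starting during the programme and persisting will be subtracted away.* Nothing says a later diary will be compared with the first. The zero in Step 2 arises only under a subtraction that the Statistical analyses section does not use.
- *That no health care use at all is recorded before randomisation.* The section on confounding and mediating variables asks about medication for several conditions, presumably at baseline, though as a possible confounder and not as a cost. Table 1, which holds the measurement schedule, is not visible. The safe statement is that no pre-randomisation resource use or cost is described.
- *That absence is the only cost component with a baseline.* HPQ productivity has one too, by the questionnaire schedule.
- *That the pre-baseline absence records are excluded from the analysis.* They have no stated use, which is weaker. A condensed article may leave covariates to the full protocol or analysis plan.

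It can also be said that adjustment is a matter of choice: chance imbalance in prior absence is already reflected in the confidence interval. That is correct. The case for adjustment rests on precision alone, at assumed correlations, for one component of a secondary economic outcome.

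**Conclusion.** The point holds in a limited form. The outcome wording for direct medical costs has no described baseline and does not match the stated analysis. The analysis is the sound part, so the wording should follow it. Correcting this changes no planned estimate and does not touch the primary outcomes or the sample size.

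The suggestion on absence costs stands on its own as an inexpensive gain: a variance cut of 9% to 25%, or an interval about 5% to 13% narrower, for an assumed r of 0.3 to 0.5. It corrects no bias, and the percentages do not carry over to total costs.

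The conclusions assume that the first diary period starts at baseline, which cannot be confirmed without Table 1, and that employer records are complete enough to serve as a covariate.

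**What to change.** 1. Under Outcome measures, confounding- and mediating variables, name the cost outcome as the between-group difference in cumulative direct, indirect and total costs over 0-12 and 0-24 months. This matches the one- and two-year economic analyses. It costs one phrase.
2. Under Statistical analyses, add that in each bootstrap replicate the absence-cost difference is estimated by regression on arm and employer-recorded absence in the six months before baseline. The planned bias corrected and accelerated interval can be kept. The covariate is already being collected. The cost is slightly more analysis work and dependence on complete employer records.

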#### Primary outcome measures

##### Body weight and BMI

Body weight and body height are assessed in all participants. Body weight is measured in kg, to the nearest 0.1 kg, with a digital scale (Seca 770; Seca GmbH & Co, Hamburg, Germany). Participants are wearing light clothing and no shoes. Body height is measured in m, to the nearest 0.001 m, with a portable stadiometer (Seca 214, Leicester Height Measure; Seca GmbH & Co, Hamburg, Germany). Positioning of the body is standardized by asking the subject to stand straight, without shoes and with the heels together. Both weight and height are measured twice, and for each mean value of the two measurements is computed. BMI is calculated by dividing the measured body weight (kg) by the squared measured body height (m).

In addition, in a questionnaire self-reported body weight is assessed. Participants are asked to weigh themselves wearing light clothing and no shoes.

##### Dietary intake and physical activity

Dietary intake and physical activity are assessed by means of a questionnaire. The focus of dietary intake is on fat, fruit and vegetable intake. Fat intake is assessed by the validated Dutch Fat List [18]. Fruit and vegetable intake are asked with a short fruit and vegetable questionnaire, that has been validated as well [19,20]. Intake of sugar and alcoholic beverages is assessed with a set of questions which were developed for this study. Physical activity level is assessed with the validated Short Questionnaire to Asses Health enhancing physical activity (SQUASH) [21].

#### Physiological outcome measures

For a random sample of each group, several additional physiological measurements are assessed in the following order: waist circumference, sum of skin folds, blood pressure, total blood cholesterol, and aerobic fitness. They are all done according to standardized protocols and take approximately 45 minutes per session.

##### Waist circumference

Waist circumference (in cm) is measured twice with a measuring tape (Gulick; Creative Health Products, Ann Arbor, MI, USA) with a range of 0–150 cm. Waist circumference is measured to the nearest 0.1 cm, at the midpoint between the lower border of the ribs and the upper border of the pelvis. A mean value of the two measurements is computed.

In addition to the objectively assessed waist circumference in the sub-sample, all 1386 employees are asked to report their self measured waist circumference in each questionnaire. For that aim, a measuring tape is sent to all participants along with the baseline questionnaire. This measuring tape is developed for the study and has a range of 0–135 cm. Participants get instructions on how to use the measuring tape and are asked to report their waist circumference to the nearest cm.

##### Sum of skin folds

According to the method of Weiner and Lourie [22] the following four skin folds are measured twice with a Harpenden caliper (HSK-BI; Baty International, Burgess Hill, UK) up to the nearest 0.1 mm and on the right side of the body: sub scapular, suprailiac, triceps and biceps. In case the two measurements of a fold differ more than 1.0 mm, the skin fold is measured a third time. Next, for each skin fold, a mean value of the measurements is computed and the four skin folds are added up.

##### Blood pressure

Blood pressure is measured with a fully automated blood pressure monitor (Omron HEM 757E [M5-I]; Omron Healthcare Europe BV, Hoofddorp, The Netherlands). This blood pressure monitor is validated and recommended for clinical use [23]. A regular size cuff is used on the right upper arm. When the subject has an upper arm circumference of 33 cm or more, a large size cuff is used. The right arm is placed on a table so as the cuff is on a level with the heart. After the employee has rested for 5 minutes in a sitting position, blood pressure is measured twice. A mean value of the two measurements is computed.

Employees that have a blood pressure of 140/90 mmHg or higher are advised to visit their general practitioner.

